### Recruitment procedure

Based on the results from preparatory studies, we developed a strategy to address and activate managers of MSE. We developed a joint communication strategy with cooperating recruitment partners (i.e., institutions and networks who support the occupational health and safety activities of MSE).

The first principle of this strategy is the digital distribution of information via email. The second principle of the strategy is cooperation with recruitment partners. Addressing employers of MSE via email is suitable, as it reaches a large sample with limited use of resources. Previous studies of the project show that employers typically obtain information on occupational health and safety topics from well-known networks and institutions, such as accident and health insurance companies. Hence, the access and communication strategy requires a close cooperation with these stakeholders (i.e. recruitment partners). We ask recruitment partners to contact MSE via email and inform them about the offer. Interested employers can follow a link to the project website, where they will learn about the advantages of stress prevention and “System P”. Each recruitment partner receives an individualized link, which allows a partner-specific analysis of the response behavior. Through the networks of our recruitment partners, we will be able to contact at least 1000 employers of MSE via email. As the recruitment partners will distribute the emails, the study team will not have access to any personal information prior to registration (e.g. names and email addresses).

Employers who fulfil the inclusion criteria will get access to the platform. They will also receive information about how to invite their employees to participate in the use of the platform. Both employers and employees can access the platform via personal accounts after a formal registration and acceptance of the terms and conditions for study participation and data protection. Employers of MSE that fulfil the inclusion criteria at registration (T0) but do not use the platform further (no login within 1 month) will be contacted again via email to fill out a short non-responder questionnaire about their socio-demographics and their reasons for not participating. To maximize the response rate, we will send a reminder via email for each questionnaire.

### Measurements

#### Primary outcome

Depression: The primary outcome measure is depression measured by the short version of the Patient Health Questionnaire (PHQ-8) at individual level [51]. The PHQ-8 contains eight items on depressive symptoms asking how often these occurred within the past 2 weeks with answers ranging from 0 “not at all” to 3 “almost every day”. The total score ranges between 0 and 24. The PHQ-scale has a good internal consistency and is sensitive to changes in mental health in clinical and non-clinical samples [52, 53].

#### Secondary outcomes

Perceived Stress: To measure the extent to which participants experience their lives as stressful we will use a German adaptation of the short version of the Perceived Stress Scale (PSS-4 [54];). It consists of four items asking respondents to rate how often they experienced stressful situations in the previous month on a five-point Likert scale ranging from 0 “never” to 4 “very often”. The scale has acceptable psychometric properties [54].

Psychosocial Safety Climate: Psychosocial Safety Climate will be measured by a German adaptation of the short version of the Psychosocial Safety Climate Questionnaire (PSC-4 [55–57];). It encompasses four items on management commitment and support, management priority, organizational commitment, and participation. Items are rated on a five-point Likert scale from 1 “strongly disagree” to 5 “strongly agree”. The scale exhibits good internal reliability and relates to a range of work conditions, health and engagement outcomes [55].

Irritation: Perceived cognitive tenseness will be assessed using the cognitive irritation subscale of the Irritation Scale, a reliable and valid measure of work-related stress that has been used across different industries and cultures [58]. The cognitive irritation subscale consists of three items on the ability to relax after work which are evaluated on a Likert scale ranging from 1 “completely disagree” to 7 “completely agree”.

Working conditions: To assess the general working conditions, we will use seven items of the German version of the Copenhagen Psychosocial Questionnaire (COPSOQ [59, 60];). Five items about working demands (e.g. “do you have to work overtime?”) and control (e.g. “can you influence the amount of work assigned to you?”) and two items on social support in the workplace (e.g. “how often do you get help from your colleagues?”) will be rated by the participants on a five-point Likert scale from 1 “always” to 5 “never”. The COPSOQ shows good reliability and validity and can by administered across a wide range of professions and industries [60].

Sickness absence and productivity loss: A German version of the second part of the questionnaire on healthcare consumption and productivity losses for patients with a psychiatric disorder (TiC-P [61];) will be used to assess sickness absenteeism and sickness presenteeism. Absence from work will be measured by three items asking for short-term and long-term absence from work. Three items assess productivity losses due to reduced efficiency during paid work while sick. The scale is a feasible and reliable instrument to assess sickness absenteeism and sickness presenteeism [61].

Harms: To assess the possibility of negative side effects of the interventions, we include one item from the Implementation Outcome Scales for Digital Mental Health (iOSDMH) [62] on harms (“This program does not result in negative side effects.”) in the follow-up questionnaires at T2 and T3.

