## Part II -Effect and process evaluation of the web-based platform “System P”

### Study design

The presented study has a type 2 hybrid design for implementation research, evaluating the effectiveness and the implementation process of the intervention at the same time [46]. We will use a one-sample repeated measures design to evaluate the effectiveness of stress prevention via “System P”. Changes in mental health and work-related stress will be measured with the help of self-rated online questionnaires administered directly via the platform (see Table 3). Measurements will take place at baseline (T1), 6 months afterwards (T2) and 12 months after baseline (T3) (see Fig. 1). The primary outcome with regard to effectiveness will be the change in self-rated depressive symptoms between T1 and T2. Additional measurements for the process evaluation will take place between the assessment points [47], with semi-structured personal interviews between T1 and T2, and focus group interviews between T2 and T3. This study protocol describes the design of the pragmatic trial based on Standard Protocol Items: Recommendations for Interventional Trials (SPIRIT) guidelines [48] (see Additional file 2).

**Table 3 Tab3:** Quantitative measures and assessment points

Questionnaire	T1	T2	T3	NR
Socio-demographic variables (age, gender, family status, first language, education, occupational position, working hours, previous contact with mental illness, income, affinity for technology), 11 items	✓	–	–	✓
Information about the organization (staff headcount, history of health program use in the organization, location, occupational sector), 4 items	✓			✓
Patient Health Questionnaire (PHQ-8), 8 items	✓	✓	✓	
Perceived Stress Scale (PSS-4), 4 items	✓	✓	✓	
Irritation (subscale cognitive irritation), 3 items	✓	✓	✓	
Psychosocial Safety Climate (PSC-4), 4 items	✓	✓	✓	
Work demands and support (COPSOQ), 7 items	✓	✓	✓	
Sickness absence and productivity (Tic-P), 6 items	✓	✓	✓	
User experience, 11 items		✓		
Readiness for change, 3 items	✓	✓	✓	✓
Harms, 1 item		✓	✓	

Note: T1 = Baseline Assessment; T2 = Post-Implementation Assessment, 6 months after T1; T2 = Follow-Up Assessment, 12 months after T1; NR = Non-Responder Questionnaire, 1 month after T0

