### Analysis

#### Sample size

Power analysis has been performed with G*Power [66] for a one sample case on the primary outcome measure depressive symptoms (PHQ score). Based on the average changes in depression reported in previous research [19, 22], we estimate a medium effect size (Cohen’s d = 0.4) [67]. With a power of 0.95 and a one-sided alpha α of 0.05, this resulted in a sample size of *n* = 70 at post-intervention measurement (T2). Due to interdependencies of the observations within MSE, we multiplied n with the design effect (DE) of cluster-randomized trials (DE = 1+ (NC-1)*ICC) [68], assuming an average cluster size (NC) of 5 (average number of employees in German MSE) and an intra-class correlation coefficient (ICC) of 0.1. This results in a required sample size of *n* = 98, and a minimum number of 20 MSE. If only 2-person MSE register (NC = 2), this would result in a required sample size of *n* = 77, equaling 39 MSE. We cannot predict the actual size of the MSE (with a range from 1 to 49 employees) and how many MSE will complete post-intervention assessment (T2) but previous studies show that only one quarter of all MSE that start interventions for stress prevention complete them [69]. The goal is therefore to recruit between 80 and 150/200 MSE for the baseline measurement. In the case of more registrations, only the first 200 MSE will be considered for the subsequent analyses.

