#### Analysis of quantitative data

To investigate the effectiveness of “System P”, the change in depressive symptoms between baseline and post-intervention assessment (T2) will be analyzed. Additionally, we will compare the change scores between individuals who completed a minimum amount of steps in the interventions (2 out of 3 steps for the PRA and 5 out of 7 steps in the SMT) and those who completed one step or less of the interventions. The effect evaluation will be performed with multilevel analysis, taking into account interdependencies at organizational level. For the quantitative process outcomes, we will calculate the average scores (e.g. for readiness for change) and average rates (e.g. penetration) and compare them across MSE with different socio-demographic characteristics.

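### The one stated harms measure, a general agreement item about the program, is likely to under-detect harm; a descriptive count of individual PHQ-8 worsening should stand beside it

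*Protocol article*

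**What the plan says.** Under Secondary outcomes, the protocol article describes the harms measure as follows: "we include one item from the Implementation Outcome Scales for Digital Mental Health (iOSDMH". The item reads "This program does not result in negative side effects" and is placed "in the follow-up questionnaires at T2 and T3". Table 3 under Study design agrees: one harms item, ticked at T2 and T3 and not in the non-responder column. The article gives neither a response scale nor a cut-off for the item, and no rule for concluding that harm is absent.

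The primary outcome, depression, is "measured by the short version of the Patient Health Questionnaire (PHQ-8) at individual level", with a score from 0 to 24. Table 3 lists "Patient Health Questionnaire (PHQ-8), 8 items" at all three time points. Under Analysis of quantitative data, "the change in depressive symptoms between baseline and post-intervention assessment (T2) will be analyzed" with a multilevel model. Change scores are also compared between people who completed a minimum number of steps and those who completed one step or less. The article mentions no count of individuals who worsen. There is no control group: "We will use a one-sample repeated measures design".

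**The concern.** The item asks for a judgement about the program in general, not about what happened to the respondent. To register harm, a person must have had a problem, traced it to the program and then disagreed with a statement worded so that agreement means no harm. Someone whose symptoms rose but who blames work or private life can agree quite honestly. A tendency to agree pushes the same way.

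A favourable average PHQ-8 change can coexist with a group of people who got worse, and neither the item nor the average would show them. The Participants section sets no exclusion on baseline symptoms, so people who already have marked symptoms may enter. What is at stake is how much the trial can say about safety. The effectiveness result is not affected.

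**Working it through.** **1. The plan's own sample size.** Inputs from Sample size: d = 0.4, one-sided alpha 0.05, power 0.95, average cluster size 5 (or 2), ICC 0.1. A one-sample t-test with the noncentral t distribution gives n = 70 (power 0.952). The design effect is 1 + (5 − 1) × 0.1 = 1.4, so 70 × 1.4 = 98. With clusters of 2 it is 1.1, so 70 × 1.1 = 77. All three figures reproduce. In information terms, 98 clustered respondents count as about 98 / 1.4 = 70 independent ones, if the ICC of 0.1 also applies to harms.

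**2. Worsening that is compatible with the planned average benefit.** Assume that PHQ-8 change is normal with a mean improvement of 0.4 SD. The article gives neither the SD of change nor a worsening threshold, so a range is shown. The probability of worsening by at least k points is 1 − Φ((k + 0.4 × SD) / SD).

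| Assumed SD of change | At least 3 points worse | At least 5 points worse | Of 98 people, at least 5 points worse |
|---|---|---|---|
| 3 | 1 − Φ(4.2/3) = 8.1% | 1 − Φ(6.2/3) = 1.9% | about 2 |
| 4 | 1 − Φ(4.6/4) = 12.5% | 1 − Φ(6.6/4) = 4.9% | about 5 |
| 5 | 1 − Φ(5/5) = 15.9% | 1 − Φ(7/5) = 8.1% | about 8 |

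The share with any increase would be Φ(−0.4) = 34.5%. That figure is a property of any normal outcome with d = 0.4. It includes measurement error and natural fluctuation, and it is not a harm rate.

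**3. What zero harm reports on the item would show.** The exact one-sided 95% upper bound is 1 − 0.05^(1/n): 3.0% at n = 98, 3.8% at n = 77 and 4.2% at the effective n = 70. It applies to respondents only, and it bounds the rate of reporting harm on this item, which may be lower than the rate of harm.

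**4. Selective response.** Suppose the true harm rate is 10% and harmed people respond r times as often as others. The rate among respondents is then 0.10r / (0.10r + 0.90): 10% at r = 1, 5.3% at r = 0.5 and 2.7% at r = 0.25. The 10% and the values of r are assumptions. The overall response rate cancels out, so the distortion depends on who drops out, not on how many. It would affect a PHQ-8 count as well as the item.

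**The case against.** The strongest reply is that the article contains no error here: the text and Table 3 agree, and a table of individual deterioration is a detail that an analysis plan or full protocol may well hold. Neither is shown, and Data Availability mentions data-monitoring guidelines on request. This stands in part. Silence in the article does not prove that worsening will go uncounted. The choice of item, its wording and its timing are fixed in the article, however, and the weakness lies there.

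A reader might infer that the trial would declare the program harmless too easily. The documents do not support that, because they state no criterion for such a conclusion.

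A reader might also take the Sample size statement that "only one quarter of all MSE that start interventions for stress prevention complete them" to mean that three quarters of participants never see the item. That figure concerns enterprises completing interventions, not individuals answering questionnaires. Reminders are planned for each questionnaire, and low users are expected among those analysed.

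PHQ-8 at T2 and T3 comes from the same questionnaires and the same respondents as the harms item, so counting worsening does not cure attrition. PHQ-8 is also a self-report, open to the social desirability that Study limitations describes. In a single-group design, worsening cannot be attributed to the program, whereas the item at least asks for attribution. These objections stand. They rule out replacing the item with PHQ-8 deterioration as the main harm indicator, but not reporting the two side by side.

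**Conclusion.** The point holds as a weakness in how harms are ascertained. The only stated measure depends on the respondent attributing a problem to the program, while individual data that could show worsening without attribution are already collected and have no stated use for harms.

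The size is illustrative. About 2% to 8% would worsen by at least 5 PHQ-8 points while the average improves as planned. This assumes normality, d = 0.4 and an SD of change of 3 to 5 points, and part of it would be ordinary fluctuation. A PHQ-8 score takes whole numbers, so the normal model is approximate. Zero reports on the item would leave an upper bound of about 3% to 4.2%, in respondents only.

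The sample size and the primary analysis are unaffected. If the unshown analysis plan already counts individual worsening, a reference to it is enough on that part.

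**What to change.** Keep the item and state its response scale and the answers that count as reporting harm. Add one descriptive harms table with:

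- the number, percentage and cluster-aware confidence interval of participants whose PHQ-8 rises beyond a reliable-change limit from T1 to T2 and from T1 to T3. The formula should be fixed in advance, for example from the trial's own T1 SD and internal consistency;
- the number without follow-up at each time point, by usage level: those who reached the minimum steps, those with one step or less, and those in between.

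State with the table that it covers respondents only, does not remove attrition bias, includes measurement error and natural fluctuation, and cannot be attributed to the program without a control group.

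The cost is one extra table from data already collected, with no new items and no change to the sample size. Its limit is that it remains descriptive.

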#### Process outcomes

Acceptability: One measurement of acceptability of stress prevention interventions is the readiness for change which will be assessed by three items adapted from Hoek et al. [63]. Items are “I believe in the value of stress prevention”, “Stress prevention is positive for the organization” and “Stress prevention is necessary” and the answers range from 1 “strongly disagree” to 5 “strongly agree”. After the implementation period, we will also measure satisfaction with the intervention by asking participants to rank the usefulness of each intervention component at T2 on a 5-point scale, with a target average score of 3 or higher.

Adoption/Reach: The proportion of MSE who adopted “System P” will be calculated by dividing the number of registered MSE at T0 by the number of invited MSE during recruitment (R1). Reach will be analyzed by comparing socio-demographic characteristics of MSE that implemented “System P” with the characteristics of non-responders (using aggregated data from the recruitment partners and data from non-responder questionnaire) to see if they are representative of the population.

Appropriateness: To gain further information on appropriateness (perceived fit for the setting), we will conduct semi-structured personal interviews with employers of MSE that are registered with inter-corporate stakeholders who are unable to contact their members via email newsletters at R1 as described above. Employers will be contacted via phone by the recruitment partners and referred to the project team. They will receive access to videos sequences introducing the web-based platform in the week prior to the interview and will then be asked about aspects that they liked and disliked as well as potential barriers for the use of the platform (the interview guide can be found in Additional file 3). The platform should be regarded as appropriate by a majority of the employers.

Fidelity: To measure fidelity, we analyze usage data collected directly via “System P”. We will track data on the times of login, number of steps completed in the web-based tool for PRA (minimum 2) and the number of completed sessions in the web-based training (minimum 5). Additionally, we will ask the participants about their use of the interventions in the online questionnaires at T2 and T3 (e.g. “How much time have you spent on average for the training?”).

Costs: The direct costs of the implementation in “System P” are none because participating organizations will not be charged for the use of the web-based platform during the study. Indirect costs will be calculated by multiplying the time spent on the platform by the average hourly salary. The hours spent logged in to the web-based platform will be monitored for employers, employee and e-coaches.

Feasibility & Sustainability: Feasibility and sustainability will be assessed by means of focus groups with a subsample of the participating MSE. All employers registered at T0 will receive an invitation to take part in the discussion about stress prevention and will be asked to describe their experience with “System P”. They will be asked to discuss barriers and facilitators for long-term implementation in their organization and suggest improvements to the web-based interventions. We will also monitor the proportion of MSE that still use the platform between T2 and T3, with a target of 20% or more.

Penetration: Penetration of the intervention within the organization will be analyzed comparing the number of registered employees who filled out the questionnaire at T1 with the number of employees reported by the employer at T1 with a target participation rate of 50% or more. We will also ask MSE during the focus groups whether new employees have received access to the platform after the implementation period to gain more information on the penetration of the interventions.

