### Implementation of interventions for occupational stress prevention

In addition to the evaluation of effectiveness, implementation research investigates the factors that affect the translation of evidence-based practices into real world settings [25]. To facilitate the implementation of stress prevention interventions in occupational settings, Nielsen and Randall [26] recommend intervention studies that include an extensive process evaluation. Proctor and colleagues [27] summarize eight outcomes for a successful implementation process: acceptability, adoption/reach, appropriateness, feasibility, fidelity/dose, costs, penetration and sustainability.

Acceptability, adoption and appropriateness are important indicators in the early phases of the implementation process. *Acceptability* is defined as the perception among stakeholders that an intervention is desirable and satisfactory [28]. It is a dynamic outcome, as acceptability can change with experience during the implementation process and can be measured with quantitative and qualitative methods. *Adoption* describes the initial decision to implement an intervention and *reach* indicates to what extent the targeted population can be reached (e.g. which MSE sign up for taking part in stress prevention programs) [29]. *Appropriateness* of an intervention describes the perceived fit of an intervention for a specific setting. It differs from acceptability as a stakeholder, e.g. an employer, and can evaluate a stress prevention program as desirable but not appropriate for their organization (e.g. due to lack of resources) [27].

Feasibility, costs and fidelity of the delivery are important indicators after the initial implementation of the intervention. *Feasibility* is related to the concept of appropriateness but measures the actual fit between the intervention and a setting rather than the perceived fit. It is usually assessed retrospectively in order to identify barriers to an effective delivery [30]. The *costs* of the intervention can be direct (e.g. purchase price of training) and indirect (e.g. time and personnel required for training) and should be measured on the side of the adopter and the provider [27]. *Fidelity* describes the extent to which an intervention was implemented as intended, for example in terms of chronological order and *dose* (amount) of the delivered components [29].

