In the second step, the results of the assessment are summarized for each item individually. A color scheme is used in which areas requiring the action of the employer are indicated in red, moderate areas in yellow, and areas with no need for action in green. This gives employers the opportunity to see which psychosocial stressors are present in their organization and to what extent. The ‘Analysis and Actions’ page also displays possible reasons for each stressor and possible actions to reduce it (employees suggestions provided during the first step and a pre-defined set of actions developed by experts based on scientific findings). Based on this information, employers can create suitable actions and document the implementation process in the tool. “System P” optionally initiates a short survey among employees to rate the potential success of a planned action before its implementation.

After a specific action has been implemented for a reasonable period of time, it is evaluated in the third step. The tool sends an automatic reminder after 3 months of implementation to remind the employer to initiate the evaluation survey. Employees can evaluate the success of the structural interventions and make suggestions for improvement. Their feedback can be used to adjust the action, develop a new one or simply document the success of the action. All steps and results are documented by the tool and can be downloaded during or at the end of the process. The duration of the whole PRA cycle depends strongly on the individual approach of the MSE and can vary between 3 months and 12 months.

*2) Web-based stress management training (“GET.ON Stress”).*

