### Study limitations

One limitation of the study is the lack of a formal control group. Due to the high heterogeneity and low implementation rate among MSE, matching the enterprises adequately poses a major challenge. We will therefore compare those MSE who completed the necessary steps for the intervention with those who did not get far in their implementation process.

Another restriction lies in the chosen method of recruitment. The number of MSE registered with the cooperating recruitment partners is limited and the response rate to the invitation emails is likely to be low. In case we are unable to reach the required sample size for the implementation study with the proposed communication strategy, we will deploy a back-up strategy that includes alternative ways to recruit MSE. The project team will prepare target-group-oriented material for advertisements in magazines, social media campaigns, and personal recommendations to support the recruitment with or without the partners. Despite increasing the chances of successful recruitment, this unstructured communication strategy will restrict the opportunity to analyze adoption and reach of the implementation.

Even though we aim to reduce stigmatized terms and to promote the acceptance of work-related stress within the “System P”, the response behavior of the participants might be affected due to social desirability [72] and fear of stigmatization [73]. Talking about stress and mental health problems in the workplace is still a major challenge. In particular, employees may be concerned about negative consequences [74] and therefore may not answer honestly the online questionnaires or refuse to participate in the workplace check. Further, social desirability and the fear of stigmatization could lead to unexplained dropouts.

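### The penetration rate and its 50% target count baseline questionnaire responders rather than employees with access to, or use of, the intervention; the adoption ratio needs a numerator matched to its denominator.

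*Protocol article*

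**What the plan says.** All three measures are in the protocol article under Process outcomes.

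- **Penetration** compares "the number of registered employees who filled out the questionnaire at T1 with the number of employees reported by the employer at T1". The target is a participation rate of at least 50%, and focus groups add a question about access for new employees. The introduction (Implementation of interventions for occupational stress prevention) defines penetration as how far the intervention is integrated into a setting, and its example is whether all employees get access. Study design makes T1 the baseline assessment.
- **Adoption** "will be calculated by dividing the number of registered MSE at T0 by the number of invited MSE during recruitment (R1"). It has no numeric target. The introduction says that adoption "describes the initial decision to implement an intervention" and illustrates reach by "which MSE sign up for taking part in stress prevention programs". Under Recruitment procedure, "Each recruitment partner receives an individualized link, which allows a partner-specific analysis of the response behavior". If recruitment falls short, Study limitations foresees "advertisements in magazines, social media campaigns, and personal recommendations to support the recruitment with or without the partners", and concedes that this would limit the analysis of adoption and reach.
- **Sustained use** is "the proportion of MSE that still use the platform between T2 and T3, with a target of 20% or more". Neither use nor the denominator is stated. Part I says that a PRA cycle "can vary between 3 months and 12 months", and Study design says that the questionnaires are delivered through the platform.

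**The concern.** For penetration, the article fixes both a formula and a target, and the formula does not match the article's own definition. Completing T1 depends on willingness to fill in a questionnaire as well as on access, and it happens before anyone can have used a component. The 50% target can therefore be missed because of poor survey response where access is wide, or met where nobody goes on to use the platform. Analysis of quantitative data also plans to compare average penetration across MSE with different characteristics, so differences in survey response would carry into that comparison.

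For adoption, the risk is a numerator that is not a subset of its denominator. For sustained use, it is a target whose meaning depends on choices the article does not state.

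The Discussion gives the implementation and effectiveness evaluations equal importance, and two of these three measures have stated targets.

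**Working it through.** **Penetration.** The 50% target comes with no derivation, so there is no figure to reproduce. Let H be headcount, R the registered employees and r the share of them who complete T1.

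- Plan's score = R × r / H
- Access = R / H
- Use = (employees who used at least one component) / H

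Take H = 5, the average MSE size in the article. R and r are assumptions, because the article gives neither.

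| R of 5 | Access | r = 40% | r = 60% | r = 80% | r = 100% |
|---|---|---|---|---|---|
| 3 | 60% | 24% | 36% | 48% | 60% |
| 4 | 80% | 32% | 48% | 64% | 80% |
| 5 | 100% | 40% | 60% | 80% | 100% |

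With four registered, the score reaches 50% only if r ≥ 0.50 / 0.80 = 62.5%. Access is 80% throughout that row, yet the result against the target changes with r alone.

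The two errors apply to different readings of penetration:

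- *Access.* Every counted T1 responder is registered, so the score cannot exceed access. It can miss the target wrongly but cannot meet it wrongly.
- *Use.* The score can meet the target wrongly. If three of five complete T1 and none opens a component, the score is 3/5 = 60% and use is 0/5 = 0%.

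**Adoption.** Let P be registrations through partner links, B registrations from elsewhere and I the invited MSE. The formula gives (P + B) / I, while the proportion of invited MSE that register is P / I. The ratio of the two is 1 + B/P. The article expects to reach at least 1000 employers by email and sets a lower recruitment goal of 80 MSE. With I = 1000 and P + B = 80, the formula gives 80/1000 = 8.0%. The split between P and B is assumed:

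- B = 0: matched proportion 80/1000 = 8.0%
- B = 20: 60/1000 = 6.0%
- B = 40: 40/1000 = 4.0%

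If only partner links produce registrations, there is no error.

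**Sustained use.** The article's planning figures reproduce: 70 × (1 + 4 × 0.1) = 98, 98/5 = 19.6, hence 20 MSE, and 20/0.25 = 80 MSE at baseline. Here the 25% completion figure is assumed to be the share of MSE still present at T2.

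| MSE at baseline | MSE at T2 | 20% of baseline | 20% of those at T2 |
|---|---|---|---|
| 80 | 20 | 16 | 4 |
| 200 | 50 | 40 | 10 |

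The number of MSE needed to meet the target differs four-fold with the unstated denominator.

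**The case against.** The strongest reply on penetration is that the article's example is access, that T1 completion by registered employees is a workable proxy for it, and that the target is openly called a participation rate. Actual use is already measured under fidelity, with minimum numbers of steps and sessions, and redefining penetration as use would blur two outcomes kept apart. This stands in part: use should not simply replace access. But the proxy adds a survey-response factor that a count of accounts would not have. Fidelity measures how much was delivered, not what share of the workforce took part.

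On adoption, much of the reply stands. Registration fits the article's definition, there is no target to miss, back-up recruitment is conditional, and its effect is conceded. A reader might infer that registration does not measure adoption at all; the definitions do not support that. What remains is that the formula has no rule for registrations from outside the invitations, although the individualized links would supply one.

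On sustained use, a fuller document could settle the threshold and the denominator. A reader might infer that T3 questionnaire logins alone would reach 20%. The article nowhere says such logins count as use, and gives no login figures.

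A reader might also infer that employees who answer the PRA through a forwarded link are missed. Part I allows the link to be forwarded, but does not say that these employees lack an account or T1 data, and Recruitment procedure has employees registering personally.

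**Conclusion.** The point holds firmly for penetration. The stated numerator is baseline survey participation, and the 50% target can be decided by questionnaire response: 48% or 64% at the same 80% access, under assumed response rates of 60% and 80%. The article gives no response or usage rates, so the actual size is unknown.

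For adoption it holds as a conditional mismatch. Its size is 1 + B/P, which is 1 if no registration comes from outside the partner invitations.

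For sustained use it is a secondary request for clarification, since the stated measure is incomplete rather than shown to be wrong.

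It would go too far to say that none of the three counts measures its outcome, or that the trial's main result is at risk. The 50% and 20% figures are descriptive targets with no test or decision attached, and neither the PHQ-8 analysis nor the sample size depends on them.

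**What to change.** - **Penetration:** report two rates over employer-reported headcount: (a) employees with a registered account, as access; and (b) employees who used at least one PRA or SMT component according to usage logs. State which of the two the 50% target applies to. Keep T1 completion as a separate survey response rate.
- **Adoption:** compute the proportion only from registrations arriving through the partners' individualized links, over MSE invited by those partners. Report registrations from other channels as counts.
- **Sustained use:** count MSE with PRA or SMT activity between T2 and T3, excluding logins made only to answer questionnaires, over MSE registered at T0. Show MSE still in their first PRA cycle separately.

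The cost is a change of definitions. Logins, PRA steps and SMT sessions are already tracked, and link source is available by design. The reported rates may be lower. PRA answers given through a forwarded link may be countable only as a total per MSE, in which case rate (b) should be shown by component.
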